#### Control group

The control arm of this trial will comprise a waiting list control where the participants randomised to the control arm will be offered the programme after approximately 10 months (after the final follow-up data collection). All study participants in both trial arms will continue to have access to a full range of locally available health and social care services including Child and Adolescent Mental Health Services (CAMHS).

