### Sample size calculation

We calculated that a sample of 676 participants was needed to detect an effect size of 0.3 with 90% power at a 5% significance level and assuming an intraclass correlation coefficient (ICC) of 0.05 [35], including 20% attrition rate. This assumed 26 clusters of 13 participants per cluster within the intervention arm (*n* = 338) and 338 participants recruited to the waiting list control arm (1:1 allocation ratio). An effect size of 0.3 on the WEMWBS is indicative of a change of 3 points on the scale stated as clinically relevant by the scale manual [36] and assuming a standard deviation of 10 as seen in a similar population [37]. For the total SDQ score, the key secondary outcome, a minimal clinically significant change is 2 as indicated by Ford and colleagues [38]. Taking a SD of 6 from normative data held by ‘*youthinmind’* [39], then an effect size of 0.33 is indicated. If the ICC is assumed equivalent to that of the parental outcome, then a sample of 676 indicates 87% power; with a reduced ICC of 0.025, this power increases to 92%.

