### Statistical and economic analysis

Analysis will be conducted on an intention to treat basis. The main analysis will be mixed effects models adjusted for baseline score, allocation group, and stratification variables. Site will be included as a random effect. To minimise bias due to missing data, predictors of missingness will be investigated using regression models and any predictors found will be considered for inclusion in the models. Multiple imputation will be employed to address missing scores where appropriate. Analysis of complete case data will be carried out as a sensitivity analysis to establish the sensitivity of the treatment effect estimates to the missing data. All treatment effect estimates will be presented with 95% confidence intervals. Additional regression analyses will explore factors associated with effectiveness. Exploratory analysis will initially look at including a measure of adherence within the models to assess the levels of effectiveness. Depending on the exact socio-demographic nature and diversity of the sample once the recruitment stage is completed, exploratory sub-group analysis will investigate different aspects of inequalities in the effectiveness of the intervention across the study population. Information with regard to data entry, coding, security, and storage is documented in a data management plan, which is available on request.

An economic evaluation will be conducted, following the recommendations of the NICE Public Health Reference Case [40]. The analysis will take a public sector perspective, estimating cost and cost effectiveness for the within-trial period. Cost effectiveness will be evaluated using a cost-utility analysis (CUA) and cost-consequences analysis (CCA). We will undertake a detailed cost analysis to estimate the costs of delivering the SFSC programme, including: development and training of accredited providers; the cost of delivering the group sessions; participant monitoring activities; and any follow-up/management. Broader resource utilisation over and above the costs of the SFSC programme will be captured via parent questionnaires administered at each data collection time point. Resource use data will be collected on NHS, social care, criminal justice system, and education contacts. Unit costs will be derived from local and national sources and estimated in line with best practice. Costs will be standardised to constant prices.

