### Process evaluation

In line with MRC guidelines [43, 44] an embedded mixed methods process evaluation will be implemented to assess intervention fidelity and provide a contextualised analysis of intervention delivery.

During the first stage of the study, the process evaluation focused on the feasibility and acceptability of the study procedures. Quantitative programme activity data was collected to assess adherence to fidelity and recruitment targets, while qualitative interviews with participants (*n* = 8) and staff (*n* = 12) were conducted to investigate the acceptability of study procedures and the recruitment and randomisation processes. We gave particular attention to attitudes towards randomisation to the waiting list control group.

During the main trial**,** the process evaluation will seek to describe the implementation of the intervention, continue to assess intervention fidelity and implement a multi-perspective qualitative investigation of intervention delivery. Routine data is collected on programme recruitment, registration, referrals, attendance, retention and staffing. Data is also collected on participation, reach, dose received (number of sessions attended), and retention rate (overall rates and in particular with reference to socio-economic position and ethnic diversity of sample). Fidelity measures are completed by staff delivering the programme at the end of each session. Additionally, an adapted version of the Parent Programme Implementation Checklist [45] will be used to assess fidelity during observation visits carried out by the research team in a random sample of programmes.

During the main trial, qualitative data collection will be extended to include individual semi-structured interviews with lead commissioners (*n* = 7) and SFSC programme coordinators (*n* = 7) across each area. In addition, we will complete individual semi-structured interviews with staff and participants, including staff involved in delivering the programme across the seven areas (*n* = 21) and participants (*n* = 20). The participants will be a purposive sample selected to represent range and diversity in terms of age of index child, ethnicity and other demographic characteristics.

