#### Progression to full trial

RAG (red/amber/green) progression criteria [47] were used to assess the randomisation, retention and intervention attendance to determine whether the stage 2 main trial could proceed (see Table 1). In line with the RAG criteria outline, ACCEPT criteria were used to determine whether pilot data could be included in the main trial [48].

**Table 1 Tab1:** RAG progression criteria

Indicator	Green	Amber	Red
Randomisation: 130 participants, either: (a) across all 5 sites/programmes OR (b) if one or two sites significantly underperforms, across the best four or three sites	More than 80%	40–80%	Less than 40%
Retention: at 3-months post intervention (around 6-months from baseline)	More than 85%	50–85%	Less than 50%
Attendance: proportion attending at least nine out of the 13 programme sessions	More than 70%	50–70%	Less than 50%
Completeness of data: on an outcome measure at baseline and post-intervention	Less than 20% missing data		
Intervention fidelity	Completion of facilitator self-assessment and quality assessment		

Based on the progression RAG criteria, progression to full trial was warranted. The total number of randomisations across the five internal pilot sites for the first 6 months of recruitment was 123, which is 95% of the target for this period and achieves a progression criterion of green. Only 14 participants withdrew from the internal pilot study prior to the 3 months follow-up. Therefore, the retention rate for the 3 months follow-up was 89% (109/123), which achieves a progression criterion of green. The median number of sessions of the SFSC programme attended by participants was 9 out of 13. The percentage of participants attending nine or more sessions was 51%, which achieves a progression criterion of amber.

Data completion - For both timepoints, and for all outcome measures the percentage of missing data was substantially less than 20%. Hence, all outcome measures are deemed acceptable for the full-scale trial.

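### The exploratory adherence model, as worded, conditions on self-selected attendance that varies only in the intervention arm, so neither its adherence term nor its arm term estimates what SFSC does

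*Protocol article*

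**What the plan says.** The section on statistical and economic analysis sets the primary approach: "Analysis will be conducted on an intention to treat basis", and "The main analysis will be mixed effects models adjusted for baseline score, allocation group, and stratification variables". Later in the same paragraph comes the adherence plan: "Exploratory analysis will initially look at including a measure of adherence within the models to assess the levels of effectiveness". It is the only adherence method that the article names.

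Three other sections determine what the sentence means in practice:

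- Process evaluation lists "dose received (number of sessions attended") among the data collected. This is a post-randomisation measure.
- Control group says that waiting-list parents are "offered the programme after approximately 10 months (after the final follow-up data collection"). No attendance is therefore planned in that arm during follow-up.
- Progression to full trial reports for the pilot: "The median number of sessions of the SFSC programme attended by participants was 9 out of 13". It also reports: "The percentage of participants attending nine or more sessions was 51" per cent. Attendance therefore varies a good deal.

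**The concern.** A covariate measured at baseline leaves the randomised comparison intact. Attendance is chosen by parents after allocation, and here only one arm can attend. Entered beside allocation, it splits the intervention arm by the parents' own behaviour and leaves the control arm whole. The adherence term is then identified only by attenders against non-attenders within one arm. With controls coded zero, the arm term becomes non-attenders (or parents at zero sessions) against all controls.

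If controls are instead left missing on adherence, they drop out of the fit and only the non-randomised comparison remains.

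About half of the pilot parents fell short of nine sessions, so what SFSC does for those who attend is a natural question. The named method cannot answer it, and it could suggest a dose-response, or hide one, for reasons unrelated to the programme.

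**Working it through.** The adherence sentence gives no figure, so there is nothing of the plan's own to reproduce. The check asks what the model would return under known truths.

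**Inputs from the article.** Share attending nine or more sessions 0.51; median 9 of 13; WEMWBS SD 10; target effect 0.3 SD (3 points), from the plan to "detect an effect size of 0.3 with 90% power at a 5% significance level"; revised allocation 360:312, so the intervention share is p = 360/672 = 0.536.

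**Assumptions, not in the article.** Engagement is a normal latent variable with correlation ρ = 0.1 to 0.3 with both baseline and follow-up WEMWBS. The baseline-outcome correlation is r = 0.5 to 0.7. Clustering is ignored, which affects standard errors more than these coefficients.

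**Step 1: what happens to the arm term.** Least squares with an intercept, arm and adherence fits both arm means exactly. Hence arm coefficient = ITT effect − (adherence coefficient × mean adherence in the intervention arm). With baseline added, this still holds in expectation. No confounding is needed for the meaning to change. Take a true ITT effect of 3 points proportional to sessions, and pilot-like attendance with mean 8.3 (simulated; median 9, 51% at nine or more). The per-session effect is 3/8.3 = 0.36, and the arm coefficient is 3 − 0.36 × 8.3 ≈ 0. The programme works, yet the arm term is null.

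**Step 2: spurious adherence effect under a true null, without baseline.** For a cut at 51%, the normal density at the cut is 0.399, so the covariance of attendance with outcome is k = 0.399ρ. The variance of attendance is v = 0.51 × 0.49 = 0.25. The coefficient is k/v. At ρ = 0.2 this is 0.0798/0.25 = 0.32 SD, with an arm coefficient of −0.51 × 0.32 = −0.16 SD.

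**Step 3: the same with the planned baseline adjustment.** Solving the two normal equations, with attendance varying only in the intervention arm and baseline in both, gives coefficient = k(1 − r)/(v − p k²).

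| ρ | unadjusted | adjusted, r = 0.5 | adjusted, r = 0.7 |
|---|---|---|---|
| 0.1 | 0.16 | 0.08 | 0.05 |
| 0.2 | 0.32 | 0.16 | 0.10 |
| 0.3 | 0.48 | 0.25 | 0.15 |

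For example, at ρ = 0.2 and r = 0.5: 0.0798 × 0.5/(0.25 − 0.536 × 0.0064) = 0.0399/0.2466 = 0.16. A simulation with 288:250 parents analysed (20% attrition) agrees with the adjusted columns to within rounding. Baseline adjustment removes half to two-thirds of the bias. What remains is 0.5 to 2.5 WEMWBS points. Reversing the sign of ρ reverses every sign in the table.

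**Step 4: does the alternative recover the truth?** A null case is no test, because the instrumental-variable estimate is the ITT difference over the attendance difference and is zero whenever the ITT effect is zero. With the 3-point effect of Step 1:

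- Number of sessions: 3/8.3 = 0.36 per session, which is the truth. In simulation it stayed at 0.36 for attendance-prognosis correlations from 0 to 0.4.
- Nine-session cut-off: 3/0.51 = 5.9 points. Parents at nine or more sessions attend 11.3 on average in this model, so their true effect is 0.361 × 11.3 = 4.1 points. The estimate is about 45% too large, because parents below nine sessions also benefit while the estimator credits everything to those above. Other pilot-like attendance shapes (53 to 57% at nine or more) give 5.3 to 5.6 points against 3.9 to 4.2, about 35% too large.

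**The case against.** The strongest reply is that the sentence fixes little. It does not define the adherence variable, the coding for controls or the estimator; it is labelled exploratory; and its word for a first step implies that more will follow. A statistical analysis plan exists but is not shown, and it may use a randomisation-based method. This stands as a limit on weight. It does not remove the point, because the article does state a method and, on its plain wording, that method puts adherence into a model alongside allocation. Exploratory status does not make the coefficient unbiased.

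Two further objections stand. First, the planned models adjust for baseline score and for stratification variables, including self-referral status, which may carry some of the engagement signal. If engagement relates to outcome only through baseline, the bias vanishes. Unadjusted figures such as 0.32 SD therefore overstate the problem for this plan. Second, the direction is unknown. The article describes referrals from social work and criminal justice; if parents with greater need attend more, the bias runs the other way.

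A reader might infer that the trial's main result is distorted, or that the adherence model is bound to manufacture a benefit. The documents support neither. The main analysis is by intention to treat and does not include adherence, and no attendance-prognosis correlation is given.

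**Conclusion.** The point holds for the exploratory adherence analysis only. As worded, that model gives an adherence coefficient that is a non-randomised comparison and an arm coefficient that no longer measures the programme's effect. The change in the arm term follows from algebra. The bias in the adherence term depends on assumptions: under a true null, with correlations of 0.1 to 0.3 and baseline adjustment (r = 0.5 to 0.7), it is about 0.05 to 0.25 SD in either direction, which is from about a sixth to over four-fifths of the 0.3 SD target. It would be zero if attendance were unrelated to prognosis given the covariates. The change is worth making because a better method is available from data already being collected.

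**What to change.** Replace the covariate model with an instrumental-variable analysis (two-stage least squares or a structural mean model) that uses randomised allocation as the instrument and keeps the baseline score and stratification covariates. Make number of sessions attended the lead exposure and state that the effect is assumed linear in sessions. Report attendance at nine or more of 13 sessions only as a secondary complier-average estimate, with the caveat that it overstates the effect if fewer than nine sessions also help. Note too that nine sessions enters the article as a pilot progression criterion, not as a definition of adherence.

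The cost is a revised sentence and a few lines of code, since attendance is already recorded. The intervals will be wider than those of the covariate model. The exclusion restriction (allocation affects outcome only through sessions attended) and the linearity assumption must both be stated.

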Outcomes for the economic evaluation will include WEMWBS (the primary outcome in the trial), the full range of secondary outcomes, and parent quality-adjusted life years (QALYs); all of these will be included in the CCA; the last of these will be used to undertake a CUA. For this, parent health-related quality of life, measured at baseline, end of programme, and 3 and 6 months post intervention using the EuroQol EQ-5D-5L will be converted into health utilities using established utility algorithms to estimate QALYs [41]. Parent-specific utility profiles will be constructed assuming a straight-line relation between each of the participant’s EQ-5D scores at each follow-up point. The QALYs experienced from baseline to final follow-up will be calculated as the area underneath this profile. We will calculate QALYs for all parents involved in the study; we acknowledge that some families in the study will be single-parent families, but the proportion of single-parent families will be similar in both trial arms. We will not include child QALYs given that some children in the trial may be as young as 3 years of age and there are no validated health-related quality of life measures in young children.

Cost effectiveness in the CUA will be calculated as the mean cost difference between the SFSC programme versus control divided by the mean difference in QALYs to give the incremental cost effectiveness ratio (ICER). We will undertake extensive sensitivity analyses. Non-parametric bootstrap estimation will be used to derive 95% confidence intervals for mean cost differences between the trial groups and to calculate 95% confidence intervals for incremental cost effectiveness ratios [42]. The bootstrap replications will also be used to construct a cost-effectiveness acceptability curve, which will show the probability the SFSC programme is cost-effective for different values of the public sector’s willingness to pay for an additional QALY. A series of deterministic sensitivity analyses will explore the implications of uncertainty on the incremental cost effectiveness ratios.

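### The cost-utility analysis is written as a mean difference in QALYs that include the baseline utility, with no stated baseline adjustment, and it promises a confidence interval for the ICER

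*Protocol article*

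**What the plan says.** All of this is in the protocol article, under Statistical and economic analysis.

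- **Measurement.** EQ-5D-5L is "measured at baseline, end of programme, and 3 and 6 months post intervention using the EuroQol EQ-5D-5L".
- **QALY.** Utilities are joined by straight lines, and "The QALYs experienced from baseline to final follow-up will be calculated as the area underneath this profile".
- **ICER.** It is "calculated as the mean cost difference between the SFSC programme versus control divided by the mean difference in QALYs".
- **Uncertainty.** "Non-parametric bootstrap estimation will be used to derive 95% confidence intervals for mean cost differences between the trial groups", and also "to calculate 95% confidence intervals for incremental cost effectiveness ratios". The same replicates feed an acceptability curve.
- **Sensitivity.** "We will undertake extensive sensitivity analyses", with no list of what these will be apart from a later mention of deterministic ones on the ICER.
- **Effectiveness, for contrast.** "The main analysis will be mixed effects models adjusted for baseline score, allocation group, and stratification variables". The text does not say that this extends to QALYs.

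The abbreviation list names an economic analysis plan, which is not available here.

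**The concern.** The article sets out the economic estimator step by step, from questionnaire to utility, to area, to ratio, and baseline adjustment is not one of the steps. Baseline utility affects the area in two ways: it has its own weight in the first interval, and it predicts every later utility. A chance difference between arms at baseline therefore reappears in the QALY difference. That difference is the denominator of the ICER, so when the true effect is small, such noise can change the size of the ratio or even its sign.

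The interval for the ratio is a separate matter. A negative ICER can mean cheaper and better, or dearer and worse. Once replicates lie on both sides of a zero QALY difference, ratios cannot be ranked in a meaningful order, and an interval built from them has no clear reading.

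**Working it through.** The article gives no QALY, cost or EQ-5D figure, so there is nothing of its own to reproduce. The check is of consequence only.

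**Inputs from the article**
- 360 intervention and 312 control parents (Impact of the COVID-19 pandemic).
- 20% attrition (Sample size calculation), carried over here to the revised sample: 0.8 × 360 = 288 and 0.8 × 312 = 249.6 analysed.
- Horizon. Table 1 puts the 3-month follow-up at around 6 months from baseline, so the final visit is at about 9 months. The Control group section implies about 10 months. An 8-week recruitment lead plus 13 weeks of programme plus 6 months gives about 11 months. End of programme is therefore set at month 3, 4 or 5.

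**Assumed, not in the article**
- Utility SD 0.15 to 0.25, equal at all visits.
- Correlation r of 0.5 to 0.7 between any two visits.

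**Formulas**
- Trapezoid weights in years for visits at t0 to t3 (months): w0 = t1/24, w1 = t2/24, w2 = (t3 − t1)/24, w3 = (t3 − t2)/24.
- SE of the baseline difference = SD × √(1/288 + 1/249.6) = SD × 0.0865.
- Slope of QALY on baseline utility: b = w0 + r(w1 + w2 + w3).
- Shift per one-SE imbalance = b × SE of the baseline difference.
- Variance factor of the area: V = (1 − r)Σw² + r(Σw)². After linear adjustment it is V − b².

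**Worked case: 10 months, SD 0.20, r = 0.6**
- Weights 0.167, 0.292, 0.250, 0.125; sum 0.833.
- SE of the baseline difference = 0.20 × 0.0865 = 0.0173.
- b = 0.167 + 0.6 × 0.667 = 0.567; shift = 0.567 × 0.0173 = 0.0098 QALY.
- V = 0.4 × 0.191 + 0.6 × 0.694 = 0.493; unadjusted SE = √0.493 × 0.0173 = 0.0121.
- Adjusted: 0.493 − 0.321 = 0.172; SE = √0.172 × 0.0173 = 0.0072, a cut of 41%.

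**Range over SD 0.15 to 0.25 and r 0.5 to 0.7**

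| Horizon | w0 (years) | Shift per one-SE imbalance (QALY) | Unadjusted SE (QALY) | SE cut by adjustment |
|---|---|---|---|---|
| 9 months | 0.125 | 0.0057–0.0122 | 0.0078–0.0144 | 32–47% |
| 10 months | 0.167 | 0.0065–0.0137 | 0.0086–0.0159 | 34–49% |
| 11 months | 0.208 | 0.0073–0.0152 | 0.0095–0.0175 | 36–50% |

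**Replicates below zero.** Take, for illustration, a true gain of 0.01 QALY. The share with a negative QALY difference is about Φ(−0.01/SE). With unadjusted SE 0.0078 to 0.0175 this is 10% to 28%. With the adjusted SE, 0.0046 to 0.0101 over the same grid, it is about 1.5% to 16%. Adjustment helps but does not by itself make the ratio interval safe.

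**Clustering, if parents were resampled individually.** Only the intervention arm is clustered, with groups of m = 6 to 13. The SE is too small by a factor √[(DE/360 + 1/312)/(1/360 + 1/312)], with DE = 1 + (m − 1) × ICC. At ICC 0.05 this gives 1.06 (m = 6) to 1.13 (m = 13), with actual coverage of a nominal 95% interval about 93.6% to 91.7%. At ICC 0.01 the factor is 1.01 to 1.03. The ICC of 0.05 was set for the parental primary outcome; none is given for QALYs or costs.

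**The case against.** The strongest reply is that a condensed article is being read too literally. A regression-adjusted difference is still a mean difference, a bootstrap by group is still non-parametric, and an area from baseline is the same outcome that an adjusted model would use. Covariates and resampling unit normally belong in an economic analysis plan; one is named but not shown, and unspecified sensitivity analyses are promised.

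Much of this stands. A reader might infer that the article commits to a raw comparison, to percentile intervals, or to a bootstrap that ignores groups. It says none of these. The silence on the resampling unit is no error. A reader might also link clustering to the baseline problem; the two are unrelated, because ignoring clustering changes interval width and the acceptability curve but not the ICER point estimate.

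Two things remain. The article does fix the form of the ICER, and it states baseline adjustment for the effectiveness models while giving an economic formula without it. And the interval for the ICER is a stated commitment, whichever interval method is used. The acceptability curve already planned supplies part of the better summary, so the second change is a modest one.

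**Conclusion.** The point holds in a limited form. If the cost-utility formula is applied as written, a one-standard-error chance imbalance in baseline EQ-5D-5L moves the QALY difference by about 0.006 to 0.015, and leaving out baseline utility forgoes a 32 to 50% reduction in standard error. These figures rest on the assumed SD and correlations, the 20% loss and a 9 to 11 month horizon.

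It would be tempting to call this a biased ICER. The documents do not support that: allocation is randomised, the imbalance averages zero, and an unadjusted interval already reflects it. What is lost is precision.

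The ICER confidence interval is likely to be hard to interpret if the effect is small; for an illustrative gain of 0.01 QALY, 10 to 28% of unadjusted replicates would fall below zero. The clustering question is secondary and is one for confirmation only.

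**What to change.** 1. State that incremental QALYs are estimated by regression on allocation with baseline EQ-5D-5L utility and the stratification variables (site, gender of parent, self-referral status), refitted within each bootstrap replicate.
2. Replace the confidence interval for the ICER with incremental net monetary benefit and its interval over a range of willingness-to-pay values, alongside the acceptability curve already planned. The ICER point estimate can still be reported.
3. Confirm that the bootstrap resamples intervention parents by SFSC group and controls individually.

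If the economic analysis plan already says this, a cross-reference is enough. Otherwise the cost is wording and code in that plan. Baseline EQ-5D-5L is already collected, and no change to sample size, visits or data collection is needed.
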